## Discussion

3

The study protocol of the proposed trial will be conducted at the second affiliated hospital of the Yunnan University of Chinese Medicine. The present study is designed to investigate whether it is feasible, effective, and safe to use massage therapy for pediatric cerebral palsy patients with basic rehabilitation treatment. If successful, the study would provide useful information for integrating massage into rehabilitation care as part of the effort of integrating Chinese and Western medicine in mainland Chinese hospitals. However, this study protocol faces several challenges and limitations.

First, patients with different types of diagnosis of children with cerebral palsy will be included, which may create variability in the population. However, Chinese medicine treatment pays more attention to syndrome differentiation rather than diagnosing disease. Also, for younger children aged <3 years, diagnosis is challenging. Moreover, randomization will be rigorous for balancing the different types of spastic cerebral palsy in the 2 groups.

Second, since this trial only involves the efficacy of massage therapy based on basic rehabilitation therapy, whether massage and basic rehabilitation therapy will form an interaction or massage therapy can be used as an alternative therapy to basic rehabilitation therapy has not been considered.

Third, the quality control of the 4 centers is particularly important, including basic rehabilitation and quality control of massage therapy. Solving this problem relies mainly on continuous training and sincere cooperation of the central treatment team, as well as establishing good relationships with the patient's family to increase compliance and follow-up.

Fourth, the choice of the control group is a difficult point in this study, although this trial is most likely to verify the clinical efficacy of massage therapy.

Currently, we cannot provide an estimate for the massage treatment costs for the treatment and control groups. It is assumed that this study can provide evidence of efficacy and high quality for the rehabilitation of cerebral palsy in children with rehabilitation and useful information for future health economic analysis. We also presume our findings to enhance the knowledge of the effectiveness of massage therapy in the hospital daily comprehensive medical practice.

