### Subject recruitment

2.3

Inclusion criteria:

(1)Aged 1 to 3 years, both male and female children.(2)Grading of the large motor function at the I-III level.^[15,16]^(3)Children who meet the diagnostic criteria for spastic cerebral palsy.^[17]^(4)Muscle tone between I-IV (according to the newly revised Ashworth scale).(5)Follow the doctor advice during the study and insist on receiving the tester.

Exclusion criteria:

(1)Those with severe mental illness and severe epilepsy.(2)Organized diseases involving other organs such as the heart, liver, and kidney.(3)Exclusion of leukodystrophy, infantile spinal muscular atrophy, spin cerebellar ataxia, genetic metabolic diseases such as phenylketonuria, congenital cretinism, and congenital hydrocephalus.(4)Failure to meet the inclusion criteria, failure to complete the test according to the regulations, and the treatment of patients who have an influence on the test results during the study, the incomplete data affect the clinical efficacy observation.(5)Spontaneous bleeding tendency.

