### Randomization and blinding

2.4

The staff member will refer to a specific random number handbook generated by an independent statistician based on statistical software before study activation to determine the study intervention assigned to the randomized patient. The randomization schedule is layered by the position of each 4-bit variable block. Participants will be randomly assigned to 1 of the 2 groups in a 1:1 ratio after completion of baseline assessment, according to a randomized block list generated by an independent research assistant using R, and the code will be kept in opaque sequentially numbered envelopes. The treatment allocation codes will be enclosed by an independent research assistant in sequentially numbered opaque envelopes and will not be revealed until the participants have completed all baseline assessments and immediately before the first massage treatment. The single-blind method is adopted in this study, and there are two-level blind methods. First, blind evaluation, in which the participants are evaluated by a third party who does not know the grouping. Second, the blind statistical analysis, where the statistical data will be analyzed by statisticians with unclear grouping and its meaning. (Fig. 1)

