### Statistical analyses^[25]^

2.12

The primary analysis will be performed using intention-to-treat methods and therefore include all randomized child data. All data will be checked into the double machine using Epidata 3.1 software for database management.

Specific statistical analysis methods: The baseline characteristics of patients in the 2 groups will be reported using frequency distribution and descriptive statistics (including measurements of concentration trends and dispersion). The main analysis of the comprehensive measurement of the rate of counting data will be the chi-square test. Two independent samples of the *t*-test will be performed between the 2 groups. The paired t-test will be used to compare the outcome variables of each treatment group before and after the treatment. The difference between the multiple measurements of the same group will be conducted using the multiple measures data analysis of variance, combined with logistic regression analysis to examine the adjustment effect of clinically relevant covariates, which will be the results (gender, birth weight, gestational age). We will also follow the pre-specified subgroup analysis. All analyses will be performed using the R software. The aforementioned steps will be monitored by the third-party tests, and the quality control of the test will be carried out. The blind law is unified and responsible.

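### The mix of spastic types is answered by randomisation alone: as described, type is balanced only in expectation and is not adjusted for in the primary comparisons

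*Protocol article*

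**What the plan says.** The first limitation in the Discussion (section 3) states that "patients with different types of diagnosis of children with cerebral palsy will be included, which may create variability in the population". The same paragraph closes with the remedy: "Moreover, randomization will be rigorous for balancing the different types of spastic cerebral palsy in the 2 groups".

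Eligibility (section 2.3, inclusion criterion 3) is narrower than the opening of that limitation: "Children who meet the diagnostic criteria for spastic cerebral palsy".

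On allocation, section 2.4 says "Participants will be randomly assigned to 1 of the 2 groups in a 1:1 ratio after completion of baseline assessment", from a block list held in opaque, sequentially numbered envelopes. Its only statement about strata is "The randomization schedule is layered by the position of each 4-bit variable block". No type of cerebral palsy is mentioned there.

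Section 2.12 plans a chi-square test for rates and an independent-samples t-test between the groups. It names three covariates (sex, birth weight and gestational age) for a logistic regression that accompanies the within-group repeated-measures analysis. It adds "We will also follow the pre-specified subgroup analysis" without naming the subgroups.

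**The concern.** The article raises a weakness and then disposes of it, so the question is whether the stated remedy does what is asked of it. Blocks of four keep the numbers in the two arms close to equal. They do nothing specific to equalise the numbers with diplegia, hemiplegia or quadriplegia. If no stratum uses type and no between-group model contains it, the remedy is chance alone.

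Type matters by the protocol's own account. The Discussion calls the mix a source of variability, and section 2.7 refers to quadriplegia and hemiplegia when it explains why lower-limb tone is used for the Ashworth outcome. If type predicts the Ashworth or GMFM score, a chance imbalance passes straight into an unadjusted t-test. Precision that adjustment could recover is also lost.

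**Working it through.** **1. The plan's own figure.** The disputed sentence carries no number, so the trial's size sets the scale. Section 2.2.1 gives 82 per group, 91 after 10% for loss, and 182 in total (two-sided α 0.05, power 0.80, absolute difference 20%). The two proportions are not stated; 0.80 versus 0.60 is assumed here:

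n = [(1.96 × √(0.70 × 0.30 × 2) + 0.84 × √(0.80 × 0.20 + 0.60 × 0.40)) / 0.20]² ≈ 81.2, rounded up to 82.

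82 × 1.10 = 90.2, rounded up to 91; 2 × 91 = 182. The figure reproduces.

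**2. Where type enters the plan.**

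| Step | Place | Type named? |
|---|---|---|
| Stratum | Section 2.4 | No; the stratum sentence is garbled |
| Between-group test | Section 2.12, t-test and chi-square | No; unadjusted |
| Named covariates | Section 2.12 | No |
| Subgroups | Section 2.12 | Not stated |

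**3. Size of chance imbalance.** Let p be the share of children with a given type. The documents give no share for the trial population. The Introduction's 52.7% diplegia refers to premature infants and serves only as an upper assumption. Without a stratum for type, the between-arm difference in shares has expectation 0 and

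SD = √(2p(1 − p)/91).

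For p = 0.20: √(2 × 0.16/91) = 0.059. For p = 0.527: √(2 × 0.527 × 0.473/91) = 0.074.

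The tail probabilities below are exact, from two independent binomials with 91 children each.

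| Assumed share | SD (points) | 95% range (points) | Gap ≥ 10 points | Gap ≥ 15 points | Gap ≥ 20 points |
|---|---|---|---|---|---|
| 20% | 5.9 | ±11.6 | 0.078 | 0.012 | 0.0006 |
| 30% | 6.8 | ±13.3 | 0.124 | 0.029 | 0.0027 |
| 50% | 7.4 | ±14.5 | 0.159 | 0.045 | 0.0059 |
| 52.7% | 7.4 | ±14.5 | 0.158 | 0.045 | 0.0059 |

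The normal approximation gives 0.18 at the 52.7% share (0.10/0.074 = 1.35). The exact value is lower because 10 points of 91 is 9.1 children, so the smallest gap that counts is 10 children, or 11.0 points.

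**4. Check by simulation.** Permuted blocks of four within four equally sized centres (both centre strata and equal sizes are assumptions; 5,000 runs per setting) gave SDs of 5.9 to 7.3 points and a chance of 9% to 16% for a gap of 10 points or more. With a two-category type added as a stratum, the SD fell to 1.4 to 1.7 points and no run reached 10 points.

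**5. From imbalance to outcome.** With two types whose mean outcomes differ by D, a gap of g in type share shifts the unadjusted group difference by g × D. A 10-point gap therefore shifts it by 0.10 × D. The documents give no D, so the shift cannot be expressed in Ashworth or GMFM points.

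**The case against.** The strongest reply is that concealed 1:1 randomisation balances every baseline factor in expectation, that the test already allows for chance imbalance, and that the Discussion promises neither a stratum nor equal shares. All of this stands. A reader might infer that the comparison is biased or that the design gives no balance by type. The documents do not support that: the scheme does balance type on average, and gaps of 20 points or more have a chance below 1%.

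Three other strong readings also fail.

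- *The scheme does not use type.* The wording in section 2.4 suggests some stratification, but the factor cannot be read from it and might be site. The full randomisation specification is not shown. All that can be said is that no stratum for type is named.
- *The described and eligible populations conflict.* The limitation opens loosely, but the objective and criterion 3 say spastic cerebral palsy, and the same paragraph ends with spastic types. This is loose drafting; eligibility is not in doubt.
- *The list must be re-stratified.* Recruitment was under way (section 4), type on top of four centres would make eight strata, and the Discussion itself says diagnosis is difficult in children under 3 years. Re-stratification is a debatable trade-off.

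It can also be said that a baseline table would show an imbalance, and that further covariates or subgroups may be set out in an analysis plan not seen here. A baseline table displays an imbalance in what was recorded; it does not adjust for it. A subgroup analysis does not adjust the main comparison either. The article does choose to name its covariates, and leaves out the one factor that its Discussion singles out.

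**Conclusion.** The concern holds in a limited form. The protocol identifies type of spastic cerebral palsy as a source of variability and, as described, relies on randomisation alone to deal with it. That gives balance in expectation, with a standard deviation of about 6 to 7 points in the between-arm difference and a chance of about 8% to 16% of a gap of 10 points or more. These figures assume 91 children per arm and type shares between 20% and 53%; a rarer type would give smaller gaps in points. The 10-point threshold is a yardstick for size and marks no known harm. The consequence is possible chance imbalance and forgone precision. The validity of the test and the sample size of 182 are untouched.

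**What to change.** - Record spastic type at baseline, for example as unilateral versus bilateral, before the envelope is opened, so that classification cannot depend on allocation.
- Add type as a pre-specified factor in the between-group model for both primary outcomes (modified Ashworth scale and GMFM), alongside the three covariates already named. For the scores, this means a model with group and covariates in place of the unadjusted t-test as the main comparison.
- Reword the first limitation in the Discussion to say that only spastic types are enrolled, and that type is balanced in expectation by randomisation and adjusted for in the analysis.
- State in section 2.4 which factor the allocation list is stratified by.

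The cost is one baseline item and one extra model term. Some very young children will be misclassified, and a two-level factor pools diplegia with quadriplegia, so some imbalance will remain after adjustment. Because type is recorded before allocation, misclassification should not differ systematically between the arms. How much precision is gained depends on how strongly type predicts the outcomes, which the documents do not say. Stratifying the remaining allocation list by type would tighten balance further but is optional.

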## Trial status

4

The first patient was recruited on June 1, 2019, and the last patient will be recruited on December 31, 2020. Patient recruitment is currently being continued
